#### 2.7.4. Head and Neck Cooling Strategy

The cooling strategy is designed to address temperature regulation in MS and provides symptomatic relief for participants experiencing thermo-sensitivity. Participants will be advised to apply a cooling cap (Headcool Power, Inuteq) to the head and neck area for a minimum of two hours daily. This cooling cap has been chosen for its effectiveness in providing targeted cooling and alleviating MS-related symptoms associated with heat sensitivity. While the study does not specify a maximum duration for the cooling strategy, the minimum duration of two hours daily is recommended to achieve optimal benefits. Regarding temperature, the cooling cap is designed to maintain a consistent cooling temperature within a comfortable range suitable for individuals with MS. The specific time of day when the cooling will be applied is not critical. However, participants will be advised to use the cooling method during their exercise sessions, when engaged in outdoor activities, and any time they do physical work that may increase their body temperature.

### 2.8. Comprehensive Assessment

To monitor progress and adjust the program as needed, participants’ functional ability, nutritional status, psychological condition, and overall quality of life will be evaluated at three key points: baseline (before starting the program), after three months, and upon completion of the program at six months.

### 2.9. Control Group—Usual Care

Participants in the control group will follow the usual care. Usual care refers to the standard care participants would receive if they were not involved in the study. This includes routine treatments and services offered in the participant’s usual healthcare setting. Participants will continue to receive their current treatment, if necessary, and may also receive additional treatments if recommended by their general practitioner or specialist due to any comorbidities. Throughout the program, participants will be encouraged to elevate their habitual levels of exercise. This encouragement will be facilitated by the utilization of a newly developed application designed to estimate participants’ exercise levels through activity tracking.

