In this light, we integrate these four components into a holistic combined rehabilitation protocol, which offers a comprehensive approach to managing MS symptoms. This holistic strategy addresses not only the physical aspects of the disease but also the emotional, psychological, and nutritional needs, thereby aiming to improve the overall quality of life for individuals with MS. The collaboration of healthcare professionals from various fields, including neurology, clinical exercise physiology, nutrition, and psychology, is vital in designing and implementing an effective rehabilitation plan. We hypothesize that compared to the control arm (usual care), Be Cool participants will show more significant improvements in the primary outcome of health-related quality of life (QoL) and in the secondary outcomes of functional ability, thermoregulation, nutritional status, mood, well-being, and psychological resilience.

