### 2.1. Eligibility Criteria

Prospective participants are eligible for the study if they meet the following criteria: they have a confirmed diagnosis of MS according to the McDonald criteria [20], exhibit the relapsing-remitting MS (RRMS) phenotype characterized by clearly defined attacks of new or increasing neurological symptoms, have experienced no relapses in the past six months, are between the ages of 20 and 60 years, have a confirmed diagnosis of MS for at least two years, and exhibit mild or moderate neurological disability, as defined by scoring between 0 to 5.5 on the Expanded Disability Status Scale (EDSS), indicating their ability to walk independently for at least 100 m without a cane [21].

The study will not include participants who have undergone psychotherapy in the past six months. Additionally, those with severe suicidality, including ideation, plan, and intent, or who have experienced one or more relapses in the previous month, have undergone corticosteroid treatment in the last month, have other severe medical conditions in addition to MS, or are currently pregnant, will not be able to participate in the study. After baseline testing, the principal investigator will perform randomization using sealed envelopes to allocate participants in a 1:1 ratio to either the BeCool or Control group.

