### 2.2. Recruitment and Trial Procedures

A promotional flyer, providing an overview of the program and contact information, was disseminated through social media channels such as Facebook, Instagram, and Twitter, as well as via email and to members of the Greek MS Society. Interested individuals were then contacted by either the Principal Investigator or representatives from the Greek MS Society’s center. Those meeting the study’s inclusion criteria were invited for a consultation, during which the study’s objectives and methodologies were explained, and a questionnaire was administered to confirm eligibility. Participants who consented to join the study attended a preliminary session for a comprehensive evaluation by a neurologist and to familiarize themselves with the experimental procedures. Subsequently, each participant was scheduled for an experimental session, which lasted for 120 min. To ensure a comprehensive evaluation of the intervention’s impact, a team of professionals from different disciplines, including clinical exercise physiology, nutrition, psychology, and environmental physiology, conduct the assessments. Enrolled participants are encouraged to continue with their usual care, which may vary based on factors such as disability status and disease severity. The usual care often includes services such as disease-modifying treatments, various aids, and physical or occupational therapy, all of which are essential for managing the condition and ensuring optimal support. However, to prevent potential confounding effects on the study outcomes, participants are advised to refrain from participating in structured exercise programs or psychological therapy during the intervention period. This ensures that any changes observed in the study are attributed specifically to the intervention being tested rather than to additional interventions that participants may undergo concurrently. Before, after three months, and after the six months of the Be Cool program, all the participants will attend an experimental session where they will undergo the following assessments.

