#### 2.7.1. Exercise Intervention and Education

The exercise program included in this intervention has been specifically designed to encourage participants to increase physical activity while reducing sedentary behaviour, thereby promoting behavioural change. Participants will engage in structured exercise sessions that are tailored to promote activity behaviour change, which may include a variety of exercises such as aerobic activities (e.g., walking, cycling), strength training, flexibility exercises, and balance training, depending on the participant’s goals and capabilities. An exercise physiologist will provide regular support and guidance to ensure that participants are on track. The exercise program will include:

Education Sessions: Participants will meet virtually with an exercise physiologist every two weeks via Microsoft Teams 24074.2321.2810.3500. During these sessions, participants will receive personalized education about their specific needs, including exercise techniques, goal setting, overcoming barriers to physical activity, and strategies for increasing daily movement and reducing sedentary time. Furthermore, the exercise physiologist will discuss the benefits of regular exercise. These benefits may include improved cardiovascular health, enhanced muscular strength and endurance, better flexibility and balance, increased energy levels, stress reduction, mood enhancement, weight management, and overall improvement in quality of life. Understanding these benefits will help participants appreciate the importance of incorporating exercise into their daily routine and motivate them to adhere to the program.

Exercise Videos: Weekly, customized exercise videos will be uploaded to the Teams platform for participants to access. These videos will provide guidance on performing exercises safely and effectively, allowing participants to engage in physical activity at their convenience while receiving ongoing support and instruction.

Mobile App Integration: A mobile app will be developed to track and monitor participants’ daily exercise levels. The app will be integrated with Google Health Fit and iOS Health Fit, allowing participants to monitor their progress, set goals, receive reminders easily, and access resources to support their physical activity progress.

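### The control arm is labelled usual care but is also encouraged to exercise more through a study app, so the contrast as written is not the one hypothesised

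*Protocol article*

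**What the plan says.** The Introduction of the protocol article sets the comparison: "We hypothesize that compared to the control arm (usual care), Be Cool participants will show more significant improvements in the primary outcome". The primary outcome is health-related quality of life, and functional ability is among the secondary outcomes.

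Section 2.9 (Control Group—Usual Care) defines the comparator: "Usual care refers to the standard care participants would receive if they were not involved in the study". Later under that heading it adds: "Throughout the program, participants will be encouraged to elevate their habitual levels of exercise". The means is also given: "This encouragement will be facilitated by the utilization of a newly developed application designed to estimate" exercise levels from activity tracking.

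Section 2.7.1 describes the exercise component of Be Cool as "specifically designed to encourage participants to increase physical activity while reducing sedentary behaviour". Among its listed parts is an app: "A mobile app will be developed to track and monitor" daily exercise.

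Section 2.1 provides for randomisation to "allocate participants in a 1:1 ratio to either the BeCool or Control group". Section 3.1 gives 15 per group at power 0.90 and α 0.05, from a G*Power repeated-measures within-between interaction with three measurement points.

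**The concern.** The definition of usual care and the encouragement sentence cannot both describe the same arm. Nobody outside the trial would receive a newly developed study app and encouragement for the length of the programme. What is added is also close to something under test, since raising physical activity is the stated aim of the Be Cool exercise component and an activity-tracking app is one of its tools.

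Two things are at stake. The first is what the trial estimates: a conclusion worded as Be Cool versus usual care would describe a comparison that was not made. The second is sensitivity. If the encouragement works at all, controls improve somewhat, and the difference in quality of life and functional ability shrinks. With 15 per group there is little room for that.

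**Working it through.** **1. The sections side by side (protocol article)**

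| Section | What it fixes |
|---|---|
| 1. Introduction | Hypothesis is against usual care |
| 2.9, definition | Control arm gets what it would get outside the study |
| 2.9, later sentences | Participants are encouraged throughout to exercise more, with a new tracking app |
| 2.7.1 | Promoting activity and tracking it by app belong to Be Cool |

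The second and third rows conflict within one section. The third and fourth overlap in aim and in type of tool. No section describes the comparator as active or restates the hypothesis against usual care plus app and encouragement.

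**2. How far the overlap goes**

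It is partial. Fortnightly education, weekly exercise videos, functional tests every three weeks with adjustment of the programme, nutrition education, ACT groups and the cooling cap are described only for Be Cool. What the control section shares is the encouragement and an activity-tracking app.

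**3. The plan's own figure**

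The 15 per group cannot be reproduced, because the article states neither the effect size f nor the correlation ρ between repeated measures. The calculation can only be run backwards.

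Inputs from section 3.1: N = 30 in total, k = 2 groups, m = 3 measurements, α = 0.05, power 0.90. Assumed: sphericity (ε = 1) and a range of ρ.

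- Noncentrality: λ = f² · N · m / (1 − ρ)
- Degrees of freedom: (k − 1)(m − 1) = 2 and (N − k)(m − 1) = 28 × 2 = 56
- Critical F(2, 56) at 0.05: 3.16
- Power of 0.90 needs λ = 13.36

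Solving for f gives 0.385, 0.322, 0.272, 0.211 and 0.172 for ρ = 0, 0.3, 0.5, 0.7 and 0.8. Check at ρ = 0.5: 0.2724² × 30 × 3 / 0.5 = 13.36.

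**4. Illustration of dilution**

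If controls gain a fraction δ of the Be Cool effect, f becomes f(1 − δ) and λ becomes 13.36 × (1 − δ)². ρ cancels, so the results hold for every ρ above.

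| Assumed δ | λ | Power at N = 30 | Total N for power 0.90 |
|---|---|---|---|
| 0% | 13.36 | 0.90 | 30 |
| 10% | 13.36 × 0.81 = 10.82 | 0.83 | 38 |
| 20% | 13.36 × 0.64 = 8.55 | 0.72 | 46 |

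A plain two-sample comparison at 15 per arm (standardised difference 1.18 for power 0.90) gives nearly the same: 0.83 at 10% and 0.74 at 20%.

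Every δ here is an assumption, and zero is within the range. Nothing in the article says how much quality of life would change through encouragement and a tracker alone.

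**The case against.** Several points on the other side have weight.

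- **Who is meant.** The sentence says only participants and refers to the programme. It may be intended for both arms or be misplaced. Its position under the control heading makes controls the natural reading, and if both arms are meant, controls still receive it. If it is misplaced, the text still needs correcting.
- **Whether it is the same app.** A reader might infer that controls get the Be Cool app with its goals, reminders and resources. The article does not say so. Section 2.9 describes only the estimation of exercise levels by tracking. The conflict with the definition of usual care does not depend on this.
- **The advice in section 2.2.** A reader might count this as a further contradiction: "participants are advised to refrain from participating in structured exercise programs or psychological therapy during the intervention period". It is not one. It concerns structured programmes, applies to all enrolled participants, and can be followed while raising habitual activity. Section 2.1 also already excludes people with psychotherapy in the past six months, so the advice on therapy probably moves the comparator little.
- **Direction of bias.** A reader might conclude that no result could be interpreted. That goes too far. Extra activity in controls would be expected to pull the difference towards zero, so on this count a positive result would be conservative. The damage falls mainly on a null result.
- **Power.** Power is lost only if the planning effect came from an undiluted contrast. The preliminary data behind it are not shown, so this cannot be settled.
- **Design choice.** Light encouragement for controls is defensible. The clear defect is that the comparator is called something else.

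These points limit the size of the concern. They do not remove the conflict within section 2.9 or the mismatch with the Introduction.

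**Conclusion.** The point holds as an inconsistency in how the comparator is defined. As written, the trial tests Be Cool against usual care plus an activity app and exercise encouragement, and the Introduction hypothesises something else. This rests on the text alone and needs no calculation.

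Some dilution is the expected direction, but its size is unknown. The fall in power from 0.90 to about 0.83 or 0.72 is conditional on three assumptions: that 15 per group is right for the undiluted contrast, that the planning effect was undiluted, and that controls gain 10% or 20% of the effect. It shows how little margin there is and does not estimate the loss.

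**What to change.** Reconcile the Introduction and sections 2.7.1 and 2.9.

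1. In the Introduction and section 2.9, name the comparator as usual care plus activity app and exercise encouragement, and word the hypothesis and the eventual conclusion to that comparator.
2. In section 2.9, state whether the encouragement and the app apply to both arms, and whether the app is the one in section 2.7.1 and with which functions.
3. Report app-recorded activity by arm as a contamination measure. This needs both arms to be recorded in the same way. It shows how far the arms separate in activity, but not how far controls moved from care without an app.
4. If the sentence was not meant for controls, delete it from section 2.9. The hypothesis can then stand as written.

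Section 2 says that participants are already being recruited. Withdrawing encouragement from controls part-way could therefore leave a control arm of about 15 with mixed exposure, which makes that route a trade-off and not a simple correction.

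The cost of naming the comparator is a wording change and one descriptive table. The downside is a narrower conclusion than one against usual care.

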### 2.10. Blinding

Randomization will be blinded to outcome assessors and the statistician. A blinded interpretation of the study results will also be conducted [29].

### 2.11. Satisfaction with the Intervention

A satisfaction questionnaire consisting of 10 questions will be sent every week to evaluate participant satisfaction with the Be Cool interventions.

### 2.12. Adherence to the Interventions

Each week, the implementers will gather attendance information from participants and ask them to rate their commitment to homework activities.

## 3. Data Analysis

### 3.1. Sample Size Calculation

Our study evaluates the effects of a holistic rehabilitation program on individuals with MS, utilizing key metrics to determine improvements in functional ability, nutritional status, and psychological well-being. Determining the minimum required sample size for our protocol was guided by preliminary data on quality of life [30]. Sample size calculations were performed using G*Power 3.0 [31], employing the “ANOVA: Repeated measures, within-between interaction” approach. This method facilitated estimating the study’s power to detect between-group differences and within-subject changes over time, considering three measurement points (baseline, mid-intervention, and post-intervention) for our MS participants. We set the statistical power and α error probability at 0.90 and 0.05, respectively, aligning with rigorous research standards to ensure sufficient sensitivity in detecting meaningful effects. Our calculations indicate that each group requires 15 individuals to power the study sufficiently. Analyses will adhere to the intention-to-treat principle, with multiple imputations used to handle missing data. A per-protocol and sensitivity analysis will also be conducted, excluding participants with significant non-compliance.

Detailed documentation and analysis of baseline demographics, including age, gender, disease duration, and relevant medical history, will provide valuable insights into the characteristics of our study population and allow us to control for potential confounding variables in our analyses. Additionally, thorough documentation of participants’ current disease-modifying therapy (DMT) regimens, including the type of medication, dosage, and duration of treatment, will enable us to assess the impact of DMT use on intervention outcomes and explore potential interactions with our intervention. We aim to conduct subgroup analyses to investigate differences in treatment effects based on baseline demographics and DMT use, with the goal of informing personalized approaches to MS management. By implementing these strategies, we aim to enhance the validity and generalizability of our findings and ultimately improve the care and outcomes of individuals living with MS.

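### One non-compliance exclusion serves as both the per-protocol and the only named sensitivity analysis; on the adherence data described it falls on Be Cool alone and does not test the imputation

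*Protocol article*

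**What the plan says.** Section 3.1 of the protocol article sets the main approach: "Analyses will adhere to the intention-to-treat principle, with multiple imputations used to handle missing data". The next sentence describes the supportive work: "A per-protocol and sensitivity analysis will also be conducted, excluding participants with significant non-compliance". It names no arm, and it gives one rule for two analyses.

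Section 2.12, the only section on adherence, says: "Each week, the implementers will gather attendance information from participants and ask them to rate their commitment to homework activities". The sessions are described in section 2.7 as parts of the Be Cool programme. For the comparator, section 2.9 says: "Participants in the control group will follow the usual care". The same section adds encouragement to be more active, with tracking by an app: "Throughout the program, participants will be encouraged to elevate their habitual levels of exercise".

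Section 2.2 places a restriction on enrolled participants without limiting it to one arm: "participants are advised to refrain from participating in structured exercise programs or psychological therapy during the intervention period".

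Section 2.10 states: "Randomization will be blinded to outcome assessors and the statistician".

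**The concern.** There are two separate problems in one sentence.

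First, the exclusion depends on what participants do after randomisation, and the adherence measures described can be scored only in Be Cool. A Be Cool participant who attends little can be identified and removed. The control participant who would have attended just as little cannot. The remaining Be Cool participants are then a selected group compared with an unselected one.

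Second, the label of sensitivity analysis is attached to a change of analysis set. The main analysis relies on multiple imputation, whose usual assumption is that values are missing at random given the observed data (the article does not say which assumption it makes). Dropping poor attenders does not vary that assumption.

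At stake is how the supportive results are read. With 15 per arm, a modest selection effect could make the per-protocol result look like confirmation of the main result, while the question a sensitivity analysis should answer stays open.

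**Working it through.** **Inputs from the article.** 15 participants per group, two-sided alpha 0.05 (section 3.1), 1:1 allocation (section 2.1).

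**Inputs not in the article, so assumed.** The number excluded from Be Cool (3 or 5 of 15), and the correlation r between compliance and outcome (0, 0.3 or 0.5). No treatment effect is assumed, so any shift is bias.

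**The plan's own figure.** The article gives no figure for this analysis. The 15 per group is used only as the arm size. It cannot be reproduced, because neither the effect size f nor the correlation among repeated measures is stated. At 30 in total, 90% power needs f = 0.385 if that correlation is 0 and f = 0.172 if it is 0.8. Nothing below depends on this.

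**Step 1: large-sample bias.** If the least compliant share q of one arm is dropped and compliance and outcome are jointly normal, the mean outcome of those kept rises by

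bias = r × φ(z_q) / (1 − q), in SD units.

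- 3 of 15: q = 0.20, z = −0.842, φ = 0.280, and 0.280/0.80 = 0.350. Bias = 0.3 × 0.350 = 0.105 SD, or 0.5 × 0.350 = 0.175 SD.
- 5 of 15: q = 0.333, z = −0.431, φ = 0.364, and 0.364/0.667 = 0.545. Bias = 0.3 × 0.545 = 0.16 SD, or 0.5 × 0.545 = 0.27 SD.
- r = 0: bias is 0 in every case.

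**Step 2: simulation at the actual arm size.** 15 per arm, t-test, 40,000 runs. The values are slightly below the large-sample formula, as expected with so few participants.

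| Dropped from Be Cool | r | Shift towards Be Cool (SD) | Two-sided type I error |
|---|---|---|---|
| 3 | 0 | 0.00 | 5.1% |
| 3 | 0.3 | 0.10 | 5.9% |
| 3 | 0.5 | 0.16 | 7.3% |
| 5 | 0 | 0.00 | 5.1% |
| 5 | 0.3 | 0.15 | 6.4% |
| 5 | 0.5 | 0.25 | 9.5% |

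**Step 3: is the asymmetry the cause?** When the same number of least compliant participants is dropped from both arms, the mean shift is within 0.005 SD of zero in every case, and type I error is 4.7% to 5.8%. So the one-sidedness produces the bias.

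**Step 4: does baseline adjustment remove it?** A separate simulation used analysis of covariance with an assumed baseline–outcome correlation of 0.5 (20,000 runs). Dropping 3 gave 0.08 SD (r = 0.3) and 0.14 SD (r = 0.5). Dropping 5 gave 0.14 and 0.22 SD, with type I error up to 9.4%. Adjustment reduces the shift somewhat but does not remove it.

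**Step 5: scale.** With 12 against 15, the standard error of the unadjusted difference is √(1/12 + 1/15) = 0.387 SD, so 0.10 SD is about a quarter of it. With 10 against 15 it is √(1/10 + 1/15) = 0.408 SD, so 0.25 SD is about 0.6 of it.

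**Step 6: the sensitivity label.** No arithmetic applies. The main analysis imputes missing values for everyone randomised. The named sensitivity analysis removes people for non-compliance. A participant can attend few sessions and still have all outcomes measured, or attend well and miss an assessment. The exclusion therefore does not vary what is assumed about the missing values.

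**The case against.** A reader might infer more than the article supports, and the opposing case is strong on several points.

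- **That non-compliers can exist only in Be Cool.** The article does not say so. The advice in section 2.2 against structured exercise and psychological therapy is not confined to one arm, so a control participant who takes up either could count as a deviator. Section 2.9 also mentions app tracking under the control group. This stands. However, no section describes recording breaches of that advice, and section 2.12 covers only attendance and homework, so on the data described the exclusion is one-sided in practice.
- **That the bias must favour Be Cool.** It does so only if compliance and outcome are positively related. The article gives no such correlation and no non-compliance rate. Removing control participants who had taken up other therapy could also move the estimate.
- **That the main result is compromised.** It is not. Intention-to-treat comes first, and a supplementary per-protocol analysis is common practice.
- **That the missing-data assumption will never be tested.** A separate analysis plan may define non-compliance and add missing-data analyses, and their absence from an article is no fault. The point rests on what is stated: the sentence says what the sensitivity analysis is, and ties it to the exclusion.
- **That attendance data will unblind the statistician.** This is speculative. Nothing says the statistician receives those data before the main analysis, and section 2.10 commits to blinding.

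At the mild end the effect is small: with 3 dropped and r = 0.3, type I error stays near nominal. The 9.5% needs a third of the arm dropped and r = 0.5.

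**Conclusion.** The point holds in a limited form. Section 3.1 uses one exclusion for two analyses with different purposes. On the adherence data described in section 2.12, that exclusion would act on Be Cool only, which gives up the protection of randomisation in the supportive comparison. Under assumed compliance–outcome correlations of 0.3 to 0.5, dropping 3 to 5 of 15 shifts the estimate towards Be Cool by about 0.1 to 0.25 SD (0.08 to 0.22 SD with baseline adjustment). With no correlation the shift is zero. The same exclusion does not test the assumption behind the multiple imputation. The intention-to-treat result stands as planned. The change is worth making because the stated method is a poor choice for its purpose and a better one is cheap.

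**What to change.** Separate the two analyses.

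1. **Sensitivity analysis.** Use delta-adjusted multiple imputation on all randomised participants. Worsen the imputed Be Cool values in prespecified steps, and report the step at which the conclusion changes. Steps of 0.2 SD up to 1.0 SD would be one example; the team should justify its own range. The effect of each step is transparent: if 3 of 15 Be Cool values were imputed, a step of 0.5 SD would move the arm mean by 0.5 × 3/15 = 0.10 SD.
2. **Per-protocol analysis.** Keep it, labelled as supplementary. Define non-compliance before unblinding, by criteria that can be applied and are recorded in both arms, including the section 2.2 restrictions on structured exercise and psychological therapy. The definition must also settle how those restrictions fit with the encouragement to exercise in section 2.9. State that this analysis will not be used to confirm or replace the intention-to-treat result.
3. **Optional.** A complier-average estimate could be added, but it should not be the replacement. With sessions attended as the measure of compliance, it assumes that allocation acts only through attendance. The cooling cap, app, exercise videos, recipes and reading material all act outside the sessions.

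The cost is revised wording, recording of deviations in the control arm, and a few hours of extra analysis. The supportive result may turn out less favourable. Sample size and treatment do not change.

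### Subgroup analyses in a trial sized at 15 per group are given the goal of informing personalised MS management, a purpose that size cannot serve

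*Protocol article*

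**What the plan says.** Section 3.1 of the protocol article gives both the sample size and the subgroup plan.

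- **Size.** "Our calculations indicate that each group requires 15 individuals to power the study sufficiently". The calculation was made by "employing the “ANOVA: Repeated measures, within-between interaction” approach", "considering three measurement points (baseline, mid-intervention, and post-intervention) for our MS participants". On the error rates: "We set the statistical power and α error probability at 0.90 and 0.05, respectively". The section calls the result a minimum. Section 2.1 says that the investigators will "allocate participants in a 1:1 ratio to either the BeCool or Control group".
- **Subgroups.** "We aim to conduct subgroup analyses to investigate differences in treatment effects based on baseline demographics and DMT use".
- **Purpose.** The same sentence continues "with the goal of informing personalized approaches to MS management".

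The section also lists baseline characteristics to be documented (age, gender, disease duration, medical history) and details of disease-modifying therapy (DMT) to be recorded (type, dosage, duration). It speaks of exploring interactions between DMT use and the intervention. The subgroup sentence itself carries no exploratory label, and the article mentions no power limit for these analyses.

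**The concern.** The sample size calculation covers one question: whether the two groups change differently over the three measurements. Asking whether the treatment effect differs between kinds of patient is a different and much more demanding question, because it compares two treatment effects, each estimated from about half the sample. The article gives that second question a purpose in patient care without noting that the trial was not sized for it.

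Two things are at stake. Real effect modification of any plausible size would usually be missed. And a contrast that did reach significance would probably overstate the true difference, yet the stated goal invites reading it as a basis for tailoring care.

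**Working it through.** **Inputs from the article:** 15 per group, 1:1 allocation, three measurements, power 0.90, alpha 0.05 (section 3.1; allocation from section 2.1). **Not given:** effect size, SD, correlation between measurements. Results are therefore in SD units, and the correlation rho is an assumption shown as a range.

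**1. The plan's own figure.** For the within-between interaction with k = 2 groups and m = 3 measurements, the noncentrality is lambda = f² × N × m / (1 − rho), with df = (k−1)(m−1) = 2 and (N−k)(m−1) = 56 at N = 30, sphericity assumed. Because f and rho are not stated, 15 per group cannot be reproduced directly. Solving backwards, N = 30 gives 90% power at f = 0.322 (rho 0.3), 0.272 (rho 0.5) or 0.211 (rho 0.7). The size is attainable and is not shown to be wrong.

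**2. Cell size.** 15 / 2 = 7.5, that is 7 or 8 patients per arm per subgroup. This assumes an even split and no dropout, which favours the plan.

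**3. Precision of the treatment-by-subgroup contrast.** The contrast is the difference between two between-arm differences, so it combines four cell means:

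SE = SD × sqrt(4 / 7.5) unadjusted, multiplied by sqrt(1 − rho²) with baseline adjustment.

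The 95% CI half-width is t(0.975, df) × SE. The detectable difference at 80% power comes from the noncentral t distribution, two-sided 0.05.

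| Model | SE (SD) | df | 95% CI half-width (SD) | Detectable at 80% power (SD) |
|---|---|---|---|---|
| Unadjusted | 0.730 | 26 | 2.056 × 0.730 = 1.50 | 2.13 |
| Adjusted, rho 0.5 | 0.730 × 0.866 = 0.632 | 25 | 2.060 × 0.632 = 1.30 | 1.84 |
| Adjusted, rho 0.7 | 0.730 × 0.714 = 0.522 | 25 | 2.060 × 0.522 = 1.07 | 1.52 |

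Power for a true interaction of 0.5 SD is 0.10 unadjusted, 0.12 at rho 0.5 and 0.15 at rho 0.7.

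**4. A comparison that needs no effect size from the sponsor.** Consider a plain comparison of the two arms at one time point. The overall SE is SD × sqrt(2 / 15) = 0.365 SD, and the difference detectable with 90% power is 1.23 SD unadjusted. With baseline adjustment it is 1.06 SD (rho 0.5) or 0.88 SD (rho 0.7). The interaction SE is exactly twice the overall SE (0.730 / 0.365 = 2). So if the treatment effect differed between subgroups by the whole of that detectable effect, power to show it would be about 37%, and this figure is the same at all three settings. If it differed by half of that effect (0.61 SD, unadjusted), power would be about 13%. To detect a 1.23 SD interaction with 90% power takes 29 per cell, or 4 × 29 = 116 patients.

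**5. Uneven split.** With 12 versus 3 per arm (80/20), the unadjusted SE is SD × sqrt(2/12 + 2/3) = 0.913 SD. Power for the 1.23 SD interaction falls to about 25%.

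**6. Multiplicity, on an assumption.** The article does not say how many factors will be tested or at what level. If five independent factors were each tested at 0.05 without adjustment, the chance of at least one false positive would be 1 − 0.95⁵ = 0.226, about 23%.

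**The case against.** The strongest reply is that the text is aspirational. It speaks of an aim and a goal, uses the language of exploration for DMT interactions, and attaches no decision rule or change in care to any subgroup result. The Discussion and Conclusions make no subgroup claim. Factor definitions, testing rules and multiplicity control commonly sit in a full protocol or analysis plan that is not shown, and the quoted phrase about differences in treatment effects is compatible with a proper interaction analysis.

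Much of this stands, and it rules out several stronger readings that a reader might infer:

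- **That the plan draws, or will report, a conclusion for care.** It states a goal only.
- **That it will form subgroups by DMT type, dosage and duration.** Those are items to be documented. The subgroup sentence says only DMT use, which could be yes/no.
- **That each listed demographic will be tested at 0.05 without adjustment.** The 0.05 belongs to the sample size calculation, so the 23% figure is conditional.
- **That subgroup results alone are said to improve validity and generalisability.** The article credits all its documentation and analysis strategies together.
- **That within-subgroup tests are planned.** The article does not say so.

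What the reply does not remove is the purpose clause. It is stated in the article, in the section that fixes the sample size, and nothing elsewhere in the article restricts these analyses to hypothesis generation. Details left to an analysis plan would not make 30 patients sufficient for that purpose.

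**Conclusion.** The point holds, confined to the stated purpose. At the planned minimum of 30 patients, a two-way subgroup contrast would have to be about 1.5 to 2.1 SD to be detectable with 80% power. Its 95% confidence interval would extend about 1.1 to 1.5 SD either side, too wide to guide the care of any kind of patient.

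These figures assume an even split, no dropout, two-sided 0.05 and, for the adjusted values, a baseline correlation of 0.5 to 0.7. Uneven splits and dropout make them worse. Final enrolment is not given, and a larger trial would do better, but about 116 patients would be needed for 90% power at an interaction of 1.23 SD.

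This does not show that the primary comparison or its sample size is wrong. Nor is the absence of subgroup definitions or a multiplicity rule from the article counted as an error.

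**What to change.** In section 3.1:

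1. Delete the goal of informing personalised management.
2. State that the subgroup analyses are exploratory and support no subgroup claim or care guidance.
3. Limit them to one or two prespecified factors from those already collected, for example DMT use yes/no.
4. Report each as an arm-by-factor interaction estimate with a 95% confidence interval in the full sample, not as separate tests within subgroups.

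The cost is a change of wording, fewer exploratory tables and a more modest stated aim. No extra patients or data are needed, and the primary analysis and sample size stay as they are.
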